### Plans to promote participant retention and complete follow-up {18b}

Information about the research trial is included on the NHS audiology service’s external website and as posters in the participating GP practices to raise awareness.

If patients report that they have not complied with advice and have not used a pretreatment wax softener, the audiology practitioner will continue to attempt to remove any wax via microsuction via routine service delivery. The data for these patients will be analysed separately from those for the other patients in an exploratory analysis.

### Data management {19}

All research data will be recorded and held on a password-protected Excel spreadsheet on the internal NHS Audiology services’ online SharePoint site, as is the current practice for service evaluation. The data will be accessible by all audiology practitioners working at the wax removal service, their service leads and the CI of the trial. There will be a focus on ensuring that the data are accurate, eligible, complete, consistent and available when needed, hence the reason for it being kept in an easily accessible location. The CI will extract the required data from the source file for analysis purposes. The data will not be shared with anyone outside the research team at any time.

A numerical identification code will be allocated to the selection of patients who consent to a video otoscopy image of their ear following microsuction. This code will be added to their corresponding data input on the main spreadsheet by the CI and on their photographic consent form. The numerical code and corresponding consent form with the patient’s name will only be available and known by the CI.

Patients will have the opportunity to share their email address to receive a summary of the trial outcomes. Their email address will not be able to be linked back to their research data entry and will be shared only with the CI. The email address will be recorded on individual GP practice patient slips alongside a GP clinic code related to the research allocation. The GP clinic codes and allocated treatment details will be stored electronically on the internal NHS Audiology online Sharepoint site in a password-protected Excel spreadsheet accessible only by the CI. This will be deleted at the end of data collection.

Both the written video otoscopy consent forms and the GP practice patient slips with completed email addresses will be stored in the research file within a locked cabinet that will be accessible only by the CI.

In compliance with good clinical practice (GCP), all documentation relevant to the trial will be retained for a period of 5 years following the end of the RCT. Further information on data management can be found within the protocol.

### Confidentiality {27}

No patient identifiable information is collected as part of this research study apart from the individuals who are selected and consent to the video otoscopy verification exercise and those who volunteer to share their email address at the end of the clinic visit to be informed of the research outcome. Both the photography consent forms and completed GP practice patient slips with email addresses will be stored in the research file in a locked cabinet at the main NHS hospital site, accessible only by the CI. Any link between codes and identifiers on consent forms will be deleted at the end of data collection.

### Plans for collection, laboratory evaluation and storage of biological specimens for genetic or molecular analysis in this trial/future use {33}

Not applicable – no biological samples are collected or evaluated in this trial.

#### Patient and public involvement

A group of five patient and public volunteers was consulted during the protocol design stage. The CI conducted two focus groups that discussed the acceptability of the research, the methodology used and the data collected. All volunteers agreed the research was worthwhile especially as the outcome may benefit patient care by potentially reducing repeated clinic visits for wax removal. They reported the methodology was acceptable and specifically supported the concept of not changing clinical practice for research purposes. Their feedback also influenced the content of the patient information material used in the study. The volunteers suggested, and we agreed to, include information on: (i) the specific type of olive oil that should be used (e.g. olive oil sold in pharmacies as opposed to ordinary ‘kitchen’ olive oil) and (ii) the number of applications of the olive oil per day. Their feedback also led to the inclusion in the protocol of a list of factors that were assumed to be random across the two groups – ethnicity, olive oil administration differences (e.g. self or assisted administration), duration of wax problems, and prior experience of wax softener use. We agreed to provide the volunteers with a summary of findings on completion of the study.

## Statistical methods

### Statistical methods for primary and secondary outcomes {20a}

Analysis and reporting of the trial will follow the Consolidated Standards of Reporting Trials (CONSORT) guidelines for cluster trials [26].

For the primary outcome analysis, a mixed effects logistic regression model will be fitted to the data with a random intercept for cluster and a fixed effect for wax softener delivery type (olive oil drops or olive oil spray) and strata (small or large GP practice). A correction factor is applied to reduce the risk of inflating the type I error rate due to the small number of clusters (< 40).

For the secondary outcomes investigating visualisation ratings and improvement in self-reported symptoms, we will use a linear mixed effects ordinal regression model with a random intercept for both clusters and patients and a fixed effect for wax softener delivery type (olive oil drops or olive oil spray) and strata (small or large GP practice). To investigate whether the reported improvement in self-reported symptoms/needs of patients who used olive oil drops significantly differed from that of patients who used olive oil spray, the unit of analysis is patient. To analyse whether there was a difference in the amount of residual wax measured by visualisation ratings between the olive oil drops and spray groups, the unit of analysis is the ear. The number of adverse events reported in the two groups will be analysed descriptively because of the likely low number of adverse events. Further details of the statistical analysis plan can be found within the protocol.

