### Participant timeline {13}

Patients are involved in the study for wax removal. The trial requires one clinic visit for every patient. Patients will be advised to use the allocated intervention for seven days prior to their appointment and then will visit the clinic for the wax removal appointment. This is shown in the trial flow chart (see Fig. 1).

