## Data collection and management

### Plans for assessment and collection of outcomes {18a}

The trial will use routine clinical data collected from patients accessing the audiology wax removal service. No additional data are collected as part of this research, which is not routinely collected for service evaluation. No patient identifiable data are collected, and all data are recorded at the microsuction appointment visit. The premicrosuction data recorded included date, location, age, referral source and self-reported presenting symptoms. The postmicrosuction data recorded included the amount of residual wax in each ear (visualisation rating) and the degree of improvement in self-reported presenting symptoms using a 5-point scale (much better, somewhat better, no change, somewhat worse, much worse). All the data are recorded during a single clinic visit.

All the data collected will be recorded on a password-protected Excel spreadsheet currently used by audiology practitioners for evaluation purposes. The spreadsheet is kept online on the Audiology SharePoint intranet site, meaning that it is accessible to all audiology practitioners working at various NHS locations.

Only patients with a complete outcome dataset were included in the final analysis.

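### As written, the symptom-improvement model has a patient random intercept but only one rating per patient, so its effect size and interval are almost undetermined

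*Protocol article*

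**What the plan says.** In the protocol article, section {20a} opens the secondary analysis with a single sentence. It covers both outcomes ("For the secondary outcomes investigating visualisation ratings and improvement in self-reported symptoms") and gives them one model, a "linear mixed effects ordinal regression model with a random intercept for both clusters and patients", with fixed effects for delivery type and practice-size stratum.

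The next sentences separate the two outcomes by unit. For symptom improvement, "the unit of analysis is patient". For residual wax, "the unit of analysis is the ear". Nothing limits the patient intercept to the second.

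On data collection, section {18a} lists residual wax for each ear but records symptoms as "the degree of improvement in self-reported presenting symptoms using a 5-point scale". It adds: "All the data are recorded during a single clinic visit". Section {13} agrees: "The trial requires one clinic visit for every patient".

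Sections {20b} and {20c} rerun the secondary analyses with age added, with a covariate for no pretreatment, and with patients who used no pretreatment removed.

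**The concern.** A patient random intercept describes correlation between several observations on one patient. Two ears give such observations; one symptom rating does not. An ordinal model also has no free residual variance, because the link fixes its scale. With one row per patient, adding a patient variance therefore does little except stretch that scale: thresholds and treatment coefficient grow together while the fitted category probabilities stay nearly the same.

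At stake is the size of the reported treatment effect on a named secondary outcome, and its confidence interval. Both would depend on a variance that the data cannot estimate. The reruns in {20b} and {20c} inherit the problem: if the fitted variance lands elsewhere in a rerun, the effect size can shift for reasons unrelated to age or adherence.

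**Working it through.** **The plan's own figure.** The article gives no figure for the symptom model. Its sample size in {14} supplies N: 26 × 67 = 1,742. That figure reproduces. The design effect is 1 + ((1 + 0.527²) × 67 − 1) × 0.02 = 2.692, the effective size per arm is 871 / 2.692 = 323.5, and 0.74 against 0.83 at two-sided 5% gives 79.7% power (pooled variance) or 80.0% (unpooled), against the stated 80%. Sidedness is not stated; two-sided was used.

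**Inputs for the check.**
- From the article: five ordered categories, one row per patient, N = 1,742, arm and stratum effects.
- Assumed: category probabilities 0.02/0.03/0.20/0.30/0.45 (set A) or 0.05/0.10/0.35/0.30/0.20 (set B), a true odds ratio of 1.5, and a stratum log odds ratio of 0.2. The practice intercept was left out to isolate the patient term.

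**Step 1, probit link.** With patient SD σ and one rating, the category probabilities depend only on the coefficient divided by √(1 + σ²). Any σ therefore fits equally well with β(σ) = β(0) × √(1 + σ²). For set A:
- σ = 0: 0.239
- σ = 1: 0.239 × √2 = 0.338
- σ = 2: 0.239 × √5 = 0.534
- σ = 3: 0.239 × √10 = 0.756

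The deviance was unchanged to six decimals throughout, so non-identification is exact.

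**Step 2, logit link.** The scaling is now approximate, β(σ) ≈ β(0) × √(1 + 0.3458σ²). Any information on σ comes only from the slight difference in shape between a logistic and a logistic-normal distribution. Fits to expected data, set A, with σ held fixed:

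| σ | Conditional odds ratio | Rise in deviance | Wald z |
|---|---|---|---|
| 0 | 1.50 | 0 | 4.42 |
| 1 | 1.62 | 0.08 | 4.42 |
| 2 | 1.90 | 0.34 | 4.40 |
| 3 | 2.31 | 0.49 | 4.39 |
| 5 | 3.56 | 0.57 | 4.38 |

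A rise of 3.84 would be needed to exclude a value at the 5% level. Set B gives odds ratios of 1.50 to 3.50 with a rise of at most 0.55.

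**Step 3, what this does to the interval.** The standard error is the log odds ratio divided by z.
- σ = 0: 0.405 / 4.423 = 0.092, so the 95% interval is exp(0.405 ± 1.96 × 0.092), about 1.25 to 1.80.
- σ = 5: 1.271 / 4.378 = 0.290, so the interval is exp(1.271 ± 1.96 × 0.290), about 2.02 to 6.30.

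The two intervals do not overlap, although the data barely distinguish the models.

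**Step 4, sampling behaviour.** In 300 simulated trials (logit link, set A, no true patient variance), σ was chosen by maximum likelihood from a grid of 0 to 5.
- The chosen σ was 0 in 47% of trials and 4 or 5 in 30%.
- The deviance range over the whole grid stayed below 3.84 in 98%.
- With the patient intercept, the odds ratio had median 1.63 and 5th–95th percentiles 1.34–4.21.
- Without it, the median was 1.50 and the percentiles 1.31–1.72.

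The grid stopped at 5, and 22% of trials chose that ceiling, so the upper percentile partly reflects the grid.

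**The case against.** The strongest reply is that the sentence is compressed. It may list the intercepts needed across two models, with the patient intercept meant only for ears, as the following sentences on units suggest. The article also refers to a fuller protocol that is not shown and may separate the models. That reading is possible, but it is not what the sentence says: it assigns both intercepts to both outcomes. This is a stated rule that does not fit one of them, not a detail left out.

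A second reply is that one rating per patient is inferred. Presenting symptoms are in the plural, and a separate rating for each would give replication. The article describes no such ratings, and the patient as unit and the single visit point the other way.

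A third reply stands: the article asks whether the arms differ significantly, and the Wald z moves only from 4.42 to 4.38. The article also names no link and no effect measure; the odds ratio is simply the usual output of a cumulative-logit model.

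Three stronger readings are tempting but unsupported:
- That the test of symptom improvement is invalid. The sign and the test are nearly unaffected.
- That the fit will fail to converge. It may, but the calculations held σ on a grid and do not show it.
- That the secondary outcomes will be tested without a small-cluster correction. {20a} states the correction for the primary outcome and is silent on the others; silence does not prescribe an uncorrected test.

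The word *linear* beside *ordinal* is loose, but *ordinal* identifies the model class and no numerical consequence follows.

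**Conclusion.** The point holds for symptom improvement only. Fitted as written, the patient variance has no replication behind it, and the conditional effect size and its interval can be badly inflated: a 5th–95th percentile range of 1.34–4.21 against 1.31–1.72 when the true odds ratio is 1.5. Non-identification is exact under a probit link and practical under a logit link at N = 1,742.

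The size rests on the assumed category probabilities, the assumed true effect, the omission of the practice intercept and the grid limit of 5. The direction does not depend on the category probabilities chosen: the second set gave almost the same spread. The conclusion also rests on one rating per patient, which is the plain but not explicit reading.

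The primary analysis, which has a cluster intercept only, is unaffected. The ear-level model for residual wax is rightly given a patient intercept.

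**What to change.** Replace the shared sentence in {20a} with two specifications:
- Symptom improvement (unit: patient): an ordinal mixed model, for example cumulative logit, with a random intercept for practice only and fixed effects for delivery type and stratum.
- Residual wax (unit: ear): the same model class with random intercepts for practice and for patient within practice.

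Use the same specifications in the reruns of {20b} and {20c}. Deleting *linear* at the same time is a tidy-up. If symptoms are in fact rated separately, say so, since a patient intercept would then have a purpose.

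The cost is wording in the protocol or analysis plan, made before analysis. Data collection, sample size and the primary analysis do not change.

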### Interim analyses {21b}

The trial includes an internal pilot that involves conducting the study as planned within a sample (10%) of the GP practices. Data will be collected as per the full study, and the Red, Amber, and Green criteria will be used. If there is less than 50% compliance (red) with the protocol, data collection will stop, and urgent training visits will be arranged to ensure that patients receive appropriate advice from healthcare professionals on the use of the allocated intervention. When compliance is between 50 and 70% (amber), data collection may be paused temporarily, and GP practices may be in contact with a research reminder. If compliance is 80% (green), data collection will continue.

A planned interim analysis involves verifying the visualisation ratings following microsuction. The audiology practitioner uses a numerical visualisation rating to categorise how much wax remains in the ear following a microsuction attempt. To verify these ratings, an anonymised photograph of the external ear canal and ear drum will be taken via a video otoscope with individual patient consent. The image is saved via a numerical code that is related to the GP practice and the age of the patient. The image is then shared with an independent experienced professional who views the image and records an independent visualisation rating. This rating will be compared with the audiology practitioner’s rating, and a Red, Amber, Green strategy (as above) will be used to validate the agreement in ratings.

There are no other formal stopping rules for the trial outside of the initial internal pilot (as described above).

### Methods for additional analyses (e.g., subgroup analyses) {20b}

Exploratory analysis of the effect of age will be performed by rerunning the primary and secondary analyses with an additional covariate of the fixed effect of age in the multilevel model.

Additionally, we expect that some patients will not adhere to the protocol and will not use any pretreatment wax softeners before attending their wax removal appointment. We will repeat the primary and secondary analyses and add a covariate fixed effect of no pretreatment used in the multilevel model. Further details can be found in the protocol.

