#### Secondary outcomes

The secondary outcomes include the following:Improvements in self-reported presenting symptoms (reported by patients during clinic visits prior to microsuction) measured via a 5-point improvement rating scale (much better, slightly better, about the same, slightly worse, and much worse) following wax removal in the two groups.Differences in the amount of residual wax following microsuction are measured by a postmicrosuction visualisation rating reported by the audiology practitioner through visual inspection of the ear. See Table 1.Adverse events. All adverse events that occur in the clinic during or immediately after microsuction and any reported by patients up to one week after microsuction, will be recorded as per normal clinical practice.

A further exploratory analysis will be completed on the following:The effect of age on the success of wax removal.Success of wax removal in patients who do not use any pretreatment.

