### Sample size {14}

A total sample size of 1,742 participants across 26 clusters/GP practices (67 participants in each practice) was calculated as sufficient to detect a minimal clinically important difference of 9%, with an 80% power level and 5% significance. The sample size for this trial was determined via ‘The Shiny CRT Calculator’ (accessible here: https://clusterrcts.shinyapps.io/rshinyapp/lculator: Power and Sample size for Cluster Randomised Trials (shinyapps.io)). The following parameters were used (trial design = parallel; correlation structure = exchangeable; differential clustering = false; allowance for varying cluster sizes = yes; coefficient of variation = 0.527; number of clusters per arm = 13; intracluster correlation = 0.02; ICC lower extreme = 0.01; ICC upper extreme = 0.05; outcome type = binary; proportion under control = 0.74; proportion under investigation = 0.83).

The above parameters were determined via discussion with statisticians and by professional consensus. A consensus was reached among 13 professionals regarding the minimal clinically important difference in the use of a specified pretreatment wax softener. The majority of the responses from the 13 professionals were between 6 and 10%, so for a conservative approach, we decided to use 9%, which was also the average.

The NHS Audiology wax removal service in North Wales is still in the process of roll out, and the actual number of GP practices participating in the study may be greater than 26. If this is the case, the sample size calculation will be reviewed.

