## Assignment of interventions: allocation

### Sequence generation {16a}

Randomisation will take place at a cluster level (GP practice) with a one-to-one allocation ratio to the two groups of olive oil drops or olive oil spray via stratified block randomisation. Stratifying was performed on the basis of site size (small, large) with block sizes of 2 and 4. A total of 26 clusters will be randomised. Randomisation is performed via the randomisation software Sealed Envelope.

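### Age is already collected and already due to be modelled, but only in an exploratory re-run; naming it in the primary model is a cheap gain in precision in a 26-practice trial (minor)

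*Protocol article*

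**What the plan says.** All references are to the Protocol article.

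- **Primary model** (Statistical methods for primary and secondary outcomes {20a}): a mixed effects logistic regression with "a random intercept for cluster and a fixed effect for wax softener delivery type (olive oil drops or olive oil spray) and strata", the strata being small and large practices. On the number of practices the section adds: "A correction factor is applied to reduce the risk of inflating the type I error rate due to the small number of clusters".
- **Randomisation** (Sequence generation {16a}): "Stratifying was performed on the basis of site size (small, large) with block sizes of 2 and 4". Practice size is the only stratification factor.
- **What is recorded** (Plans for assessment and collection of outcomes {18a}): "The premicrosuction data recorded included date, location, age, referral source and self-reported presenting symptoms".
- **Role of age**: Secondary outcomes lists, as an exploratory question, "The effect of age on the success of wax removal". Methods for additional analyses {20b} says how it will be answered: "Exploratory analysis of the effect of age will be performed by rerunning the primary and secondary analyses with an additional covariate".
- **Referral source** is in no model that the article describes.

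**The concern.** The randomised unit is the practice, and there are 26 of them. For any characteristic that differs between practices, balance depends mainly on 13 against 13 and much less on the 1,742 patients. Stratifying on practice size does nothing direct for age. If age predicts successful clearance and varies between practices, the arm-plus-stratum model leaves that variation in the between-practice error. Any age difference between the arms that chance produces then stays in the headline estimate.

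What is at stake is efficiency and how well the estimate fits the practices actually drawn; validity is not in question. The article fixes both the covariates of the primary model and the exploratory status of age, so this is a stated choice. It is not a gap left to a fuller document.

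**Working it through.** **1. The plan's own figure.** Sample size {14} gives "number of clusters per arm = 13; intracluster correlation = 0.02", 67 patients per practice, a coefficient of variation of cluster size of 0.527, and success of 0.74 against 0.83. Two-sided 5% is assumed, because sidedness is not stated.

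- Design effect = 1 + ((1 + 0.527²) × 67 − 1) × 0.02 = 2.692.
- Patients per arm = 13 × 67 = 871.
- SE of the difference = √(2.692 × (0.74 × 0.26 + 0.83 × 0.17) / 871) = 0.0321, or 3.2 points.
- Power = Φ(0.09/0.0321 − 1.96) = 0.80.

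The smallest cluster size that reaches 80% is 67, so 1,742 is reproduced. The calculation includes no covariate adjustment. With the same design effect and a t reference on 24 df, power is 0.767, so there is little slack once a small-cluster correction is applied.

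**2. How far the arms can differ in mean age by chance.** The article gives no age SD and no age ICC; both are assumed. SD of the arm difference = age SD × √(2 × DE/871), where DE is the design effect above with the age ICC in place of 0.02. For an age SD of 15 years:

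| Age ICC | DE | SD of difference (years) | 95% range (± years) |
|---|---|---|---|
| 0.02 | 2.69 | 1.18 | 2.3 |
| 0.05 | 5.23 | 1.64 | 3.2 |
| 0.10 | 9.46 | 2.21 | 4.3 |

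**3. What that does to the estimate.** Shift ≈ ln(OR per decade) × (age difference/10) × p(1 − p). With p = (0.74 + 0.83)/2 = 0.785, p(1 − p) = 0.169. For a 1-SD imbalance, in percentage points:

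| Age ICC | OR 1.1 | OR 1.25 | OR 1.5 |
|---|---|---|---|
| 0.02 | 0.19 | 0.44 | 0.81 |
| 0.05 | 0.26 | 0.62 | 1.12 |
| 0.10 | 0.36 | 0.83 | 1.51 |

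Widening the assumptions to an age SD of 12 to 18 years and an ICC of 0.01 to 0.10 gives about 0.1 to 1.8 points for a 1-SD imbalance. The like-for-like yardstick is the SE of 3.2 points. The 9-point target is not the right comparison.

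**4. Effect on error rate and power.** This was simulated with 26 practices, age SD 15 and age ICC 0.02, 0.05 or 0.10, comparing cluster-level t tests with and without age adjustment (3,000 runs per null setting, 2,000 per power setting).

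- Under no effect, both estimates centre on zero. Across odds ratios of 1.0 to 1.5, rejection is 4.4 to 6.2% unadjusted and 4.4 to 6.4% adjusted.
- Power, unadjusted → adjusted:

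| Age ICC | OR 1.1 | OR 1.25 | OR 1.5 |
|---|---|---|---|
| 0.02 | 0.847 → 0.848 | 0.836 → 0.846 | 0.812 → 0.841 |
| 0.05 | 0.849 → 0.844 | 0.850 → 0.858 | 0.805 → 0.841 |
| 0.10 | 0.847 → 0.850 | 0.833 → 0.852 | 0.774 → 0.844 |

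Read the differences and not the levels. The simulated levels sit somewhat above the 0.80 of step 1, and the simulation uses a two-stage cluster test in place of the planned mixed model. The largest gain, 7.0 points, is mostly recovery: strongly prognostic, clustered age lowers unadjusted power to 0.774, and adjustment restores it.

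**The case against.** The strongest reply is that nothing here is an error. The model adjusts for the one stratification factor, has a practice-level random intercept and corrects for few clusters. Chance imbalance in age is random error that the confidence interval already covers, and step 4 shows no bias and no inflation. **This stands.** A reader might infer that leaving age out biases the main result; the documents and the simulation do not support that.

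Other stronger readings also fail:

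- *An age-adjusted result would be post hoc.* It would not, because the re-run is specified in advance. What is open is only which of two planned models leads.
- *The plan assumes age is balanced.* The section on patient and public involvement does mention "a list of factors that were assumed to be random across the two groups", but those are ethnicity, how the oil is applied, duration of the wax problem and earlier softener use. Neither age nor referral source is among them.
- *The plan expects age to matter.* It poses an exploratory question and states no expectation. Nor does it say that age varies between practices.
- *Referral source must be adjusted for too.* The rationale describes self-referral and professional referral, but nothing ties the route to success of microsuction.

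Two practical objections carry some weight. Recruitment began on 1 January 2025, so the change would alter the primary model during the trial. And because only patients with a full dataset are analysed, a new primary covariate could remove patients.

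The objections do not remove the case for acting: the variable is already collected, the model is already planned, and the reordering has no error-rate cost in the simulation.

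**Conclusion.** The point holds as a minor, nearly free improvement and is not a flaw in validity. The primary analysis is sound under chance imbalance. By confining age to an exploratory re-run, the plan forgoes precision that may be trivial or may reach about 7 points of power. Which of these applies depends on an age SD, an age ICC and an age effect that the documents do not give. If age is only weakly related to success (odds ratio 1.1 per decade), the change makes no detectable difference to power. If it is strongly related (1.5), the gain is about 3 points at an age ICC of 0.02 and about 7 at 0.10.

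**What to change.** Before the data are analysed, and without reference to outcomes by arm:

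1. Name age, as a continuous fixed effect, in the primary model and in the two secondary ordinal models.
2. Report the arm-plus-stratum model as the sensitivity analysis.
3. State how a record without an age will be handled, so that the full-dataset rule does not drop a patient whose outcome is known.
4. Treat referral source as optional.

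**Cost.** No new data are needed. The odds ratio becomes conditional on age and should be labelled so. Because the trial is under way, the change has to pass through the amendment route in section {25}, which requires sponsor and ethics approval. If the team prefers to keep the present primary model, the smaller step is to promote the age-adjusted model from exploratory to a named sensitivity analysis of the primary outcome. That settles the model's status in advance but does not bring the precision gain into the main result.
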